**STATEMENT OF COMPLIANCE**

This study will be conducted in compliance with the applicable principles and regulatory requirements from the United States Code of Federal Regulations (CFR), including 21 CFR 56 (institutional review board [IRB]) and 21 CFR 50 (informed consent) and to the principles outlined in applicable ICH guidelines.

## LIST OF ABBREVIATIONS

|         |                                                 |
|---------|-------------------------------------------------|
| AB      | antibiotic                                      |
| AE      | adverse event                                   |
| AS      | antibiotic stewardship                          |
| CAP     | community-acquired pneumonia                    |
| DASON   | Duke Antimicrobial Stewardship Outreach Network |
| DCRI    | Duke Clinical Research Institute                |
| DICON   | Duke Infection Control Outreach Network         |
| DOCR    | Duke Office of Clinical Research                |
| DOT     | days of therapy                                 |
| EHR     | electronic health record                        |
| HCAP    | healthcare-associated pneumonia                 |
| IDSA    | Infectious Diseases Society of America          |
| IRB     | institutional review board                      |
| MRN     | medical record number                           |
| PAR     | post-antibiotic prescription review             |
| PI      | principal investigator                          |
| TMP-SMX | trimethoprim-sulfamethoxazole                   |
| UTI     | urinary tract infection                         |

103 **PROTOCOL SYNOPSIS**

104

|                                        |                                                                                                                                                                                                         |
|----------------------------------------|---------------------------------------------------------------------------------------------------------------------------------------------------------------------------------------------------------|
| Protocol Title:                        | A Multicenter, Three-Stage Cluster-Randomized Historically Controlled Crossover Trial to Determine the Feasibility and Outcomes from Two Antimicrobial Stewardship Interventions in Community Hospitals |
| Phase:                                 | Not Applicable                                                                                                                                                                                          |
| Products:                              | Not Applicable                                                                                                                                                                                          |
| Objectives:                            | To evaluate the feasibility of implementing antimicrobial restriction and preauthorization vs. prospective audit and feedback in resource-limited community hospitals                                   |
| Study Design:                          | Three-stage cluster-randomized historically controlled crossover trial                                                                                                                                  |
| Study Population:                      | Patients who receive targeted or alternative antimicrobials, hospitalized in one of the four community hospitals                                                                                        |
| Number of Participants:                | Not Applicable                                                                                                                                                                                          |
| Number of Sites:                       | 4                                                                                                                                                                                                       |
| Duration of Participant Participation: | Participation is at the hospital level. All hospitals will participate for 13 months.                                                                                                                   |
| Dose Schedule:                         | Not Applicable                                                                                                                                                                                          |
| Estimated Start:                       | August 1 st 2014                                                                                                                                                                             |
| Estimated Time to Complete Enrollment: | 13 months for study duration                                                                                                                                                                            |

105

106 **STUDY DESIGN SCHEMA**

[figure not shown]

## STUDY DESIGN POPULATION

[figure not shown]

## 2 BACKGROUND INFORMATION AND SCIENTIFIC RATIONALE

### 2.1 Background Information

Hospitals in the United States have observed increasing rates of drug-resistant pathogens and healthcare facility associated *Clostridium difficile* infection, leading to significant burdens of morbidity, mortality, and hospital costs. A causal relationship between antibiotic exposure and acquired drug resistance is well established. However, 30% to 50% of antibiotic use in US hospitals is inappropriate. Hospital-level quality improvement programs to improve antibiotic stewardship (AS) are an essential intervention to curb these concerning trends.

### 2.2 Scientific Rationale

The Infectious Diseases Society of America (IDSA) guidelines recommend two “core” strategies for AS: 1) antimicrobial restriction and preauthorization and 2) prospective audit with intervention and feedback. Community hospitals have limited or no resources and staff dedicated to AS. Thus, understanding which of the core strategies is most effective in this practice setting would assist in appropriate allocation of limited resources.

### 2.3 Potential Risks and Benefits

#### 2.3.1 Potential Risks

Potential risks are minimal due to the fact that all patients will continue to receive treatment per usual care. This study will provide an extra level of examination into the appropriateness of the prescribed antibiotic through AS interaction of prescribing physicians with trained pharmacists.

#### 2.3.2 Benefits

Patients may benefit from having more attention paid to the course of treatment for their infections. Patients may receive more appropriate antimicrobial treatment, including using appropriate antimicrobial agents when an infection is present and stopping antimicrobial agents when they are unnecessary.

### 3 OBJECTIVES

The purpose of this study is to evaluate the feasibility of implementing antimicrobial restriction and preauthorization vs. post antibiotic prescription review in resource-limited community hospitals.

#### 3.1 Study Hypotheses and Objectives

##### 3.1.1 Hypotheses

- Primary Feasibility Hypothesis

The protocol of two stewardship strategies [Antimicrobial restriction and preauthorization and post-antibiotic prescription review] will receive approval at hospitals. The two stewardship strategies will both be successfully implemented, including training of local pharmacists (PharmDs), at all four hospitals.

##### Secondary Stewardship Hypotheses

1. Antimicrobial restriction and preauthorization will be less resource-intensive for hospitals (e.g., set-up time, approval time, personnel resources) than post-antibiotic prescription review (PAR) and feedback.
2. Prescribers will consider preauthorization to be intrusive to clinician autonomy and patient care.
3. The cost of performing PAR by a trained pharmacist will be offset by the cost savings achieved by decreasing antimicrobial cost.
4. Both strategies will lead to a decrease in utilization for targeted antimicrobials relative to utilization in the period prior to implementation of the stewardship strategies.
5. Decreases in targeted antimicrobial utilization from antimicrobial restriction will be offset by increases in use of alternative antibiotics.
6. The strategy of antimicrobial restriction and preauthorization will be less effective at reducing overall antimicrobial use than the strategy of prospective audit and feedback, as it will not shorten duration of antimicrobial therapy.

##### 3.1.2 Primary Objectives

##### Feasibility Objectives

1. To evaluate having the protocol of two stewardship intervention strategies approved by hospital administration and committees
2. To evaluate the training of local PharmDs in administration of the two stewardship strategies

3. To evaluate the initiation and implementation of the two stewardship strategies at four hospitals

### 3.1.3 Secondary Objectives

To estimate and compare the time required of the pharmacist to administer each strategy

1. To estimate and compare the resource utilization of each strategy, where resource utilization includes pharmacist time and cost of antibiotics.
2. To compare the days of therapy (DOT) for antibiotics of interest between each strategy  
DOT will be measured as the number of days a patient receives each targeted and alternative antibiotic during the hospital admission.
3. To compare patient-specific outcomes between each strategy, including but not limited to the following:
  - a. Total hospital days
  - b. Death
  - c. Intensive care unit admission
4. To compare the prescriber and pharmacist perceptions of the two stewardship strategies
5. To develop integrated measures of benefit: risk for AS (based on days of therapy, hospital days, and patient outcomes such as ICU admission and survival) and compare strategy effects with respect to these measures

### 3.1.4 Exploratory Objective

To evaluate the interpretations reached from analysis of data based on traditional (DOT/patient-days) outcomes as compared to newer proposed outcomes (defined in Section 3.1.3 Secondary Objectives, number 5).

## 4 STUDY DESIGN

This study is a three-stage cluster randomized historically controlled crossover trial designed to evaluate the feasibility of the implementation of two AS strategies. Data will be obtained from four community hospitals in three stages. In stage 1, historical data from each hospital will be collected for the year prior to study initiation from all participating hospitals. These data are used as a control representing current practice. In stage 2, the four hospitals will be divided into two pairs based upon bed size. One hospital from each pair will be randomly assigned to a six-month period of antimicrobial restriction and preauthorization (Strategy 1; stage 2) followed by a six-month period of post-antibiotic prescription review (Strategy 2; stage 3). The other two hospitals will undergo Strategy 2 in stage 2 followed by Strategy 1 in stage 3 to help alleviate the concern for seasonal/temporal effects when comparing the strategies to each other. Temporal/seasonal effects are not controlled when comparing to the historical control. A one-month wash out will be performed between each stage. Three antibiotics will be specifically targeted for intervention: anti-pseudomonal carbapenem of choice at the study hospital, vancomycin, and piperacillin-tazobactam. Utilization of alternative antimicrobials, including fluoroquinolones, cephalosporins, and anti-methicillin-resistant *Staphylococcus aureus* (anti-MRSA) systemic antimicrobials (e.g., nafcillin, daptomycin, linezolid, ceftaroline, clindamycin, and trimethoprim-sulfamethoxazole [TMP-SMX]) will also be collected.

### 4.1 Study Population

#### 4.1.1 Selection of the Study Population

Four community hospitals in the Duke Infection Control Outreach Network (DICON) will be recruited for this study. Ideally, hospitals will have no teaching affiliation, bed size <300, and no existing antimicrobial formulary restriction and preauthorization or PAR practices in place at study start.

Drug use Identification: All study hospitals will have electronic systems that track antimicrobial prescriptions through orders, electronic medication administration records (eMAR), bar-coded medication administration (BCMA), or dispensing data.

#### 4.1.2 Inclusion/Exclusion Criteria

Inclusion criteria: All adult and pediatric patients admitted to the study hospital who are prescribed targeted or alternative antimicrobial agent(s) will have data collected from their medical records.

Exclusion criteria: Any patient not meeting the criteria above will be excluded. Patients who receive < 24 hours of surgical prophylaxis with a targeted or alternative antimicrobial will be excluded.

### 4.1.3 Treatment Assignment Procedures

The four hospitals will be divided into two pairs based upon bed size and in discussion with the protocol team. One hospital in each pair will implement Stewardship strategy 1 followed by Stewardship strategy 2. The other hospital in each pair will implement Stewardship strategy 2 followed by Stewardship strategy 1. The order of the strategies will be randomly generated at the SDMC and communicated to the local PharmD and pre-identified hospital staff.

### 4.1.4 Stewardship Strategy Descriptions

Hospitals will have dedicated clinical pharmacist time for preauthorization or post-antibiotic review for the three targeted antibiotics in each arm of the study. One PharmD at each site will receive standardized training by study personnel in order to address common questions and anticipated arguments, and to establish a robust knowledge base regarding the targeted antimicrobials (anti-pseudomonal carbapenem of choice at the study hospital, vancomycin, and piperacillin-tazobactam). They will also be trained in conflict management.

Study personnel will provide suggested criteria for appropriate use of each targeted drug. Hospital P&T committees will review, edit (if desired), and approve hospital-specific protocols for appropriate use criteria for each study drug. On-site pharmacists will then use the local criteria to determine whether each prescription falls into protocol vs. non-protocol use and then recommend approval/disapproval and/or alternative therapy to the prescriber in real time.

Each participating pharmacist will be thoroughly trained by study staff prior to the study. Pharmacists will be provided with specific clinical pathways for urinary tract infections (UTIs), community-acquired pneumonia (CAP), healthcare-associated pneumonia (HCAP), bacteremia, and “other” uses of targeted antimicrobial. Clinical pathways will be developed jointly by study personnel and based on Centers for Disease Control and Prevention pilot projects. Clinical pharmacists will determine appropriateness of therapy based on study clinical pathways, their baseline knowledge, and acquired knowledge derived by training from study personnel. Time spent performing the two stewardship strategies will be supported by grant funds. The designated pharmacist will be involved in two critical components of the protocol: a) completing the intervention and b) documenting the outcome of the intervention.

Stewardship Strategy 1 – Antimicrobial restriction and Pre-authorization. Following approval of the protocol at study hospitals, all prescriptions for targeted antibiotics will require phone approval by the trained PharmD. Prescribers will be instructed to discuss the patient details and the rationale for the desired antimicrobial with the PharmD. Specifically, prescribers must contact the pharmacist via pager or phone call to discuss the rationale for using the targeted antibiotic. The pharmacist will discuss the rationale and the specific clinical scenario with the prescriber and will decide if the targeted antibiotic is approved or denied. If the pharmacist denies the use of the targeted antibiotic, the pharmacist will provide recommendations for alternative antibiotics for the specific clinical scenario. The pharmacist will then document this interaction in the REDCap database, documenting which targeted antibiotic was requested, the prescriber’s rationale for requesting the targeted antibiotic, the patient’s symptoms and pertinent

clinical data at the time of the request, whether the request met the criteria for use of the targeted antibiotic (or not), and the pharmacist's recommendation. Prescriptions for targeted antibiotics will be eligible for intervention if written between 7am and 6pm Monday through Friday. Off-hours prescriptions will be reviewed for approval for continuation the following morning.

Stewardship Strategy 2 – Post-antibiotic Review and Feedback. Following approval of the protocol at study hospitals, all prescriptions for targeted antibiotics will be reviewed by the study pharmacist approximately 72 hours after initially written. The clinical pharmacists will review a list of patients receiving the targeted antibiotics on a daily basis to identify patients who have received one or more targeted antibiotics for 72 hours ( $\pm$  24 hours). The pharmacist will review and document the patient's current symptoms, pertinent clinical data, and the indication for the targeted antibiotic documented in the chart. Based on this review, the pharmacist will decide if the targeted antibiotic is necessary and/or if it needs to be modified. If a change is recommended, the pharmacist will then contact the prescriber (i.e., by pager, by phone call, or during clinical rounds) to discuss the pharmacist's recommendations. The interaction will be documented in the REDCap database, including whether or not the prescriber is going to follow the pharmacist's advice. If the pharmacist concludes that the antibiotic is appropriate, then he or she will document that the antibiotic is appropriate but will not be required to contact the prescriber.

Follow up: Strategy 1 and Strategy 2 -- For both strategies, the pharmacist will review the patient's chart approximately five days after interacting with the prescriber to document whether the pharmacist's recommendation was followed. The pharmacist will specifically document if the recommendation was followed, the recommended duration of antibiotic, whether the dose of the antibiotic was appropriate, and the ultimate infection diagnosis. If the patient has already been discharged, the pharmacist will review the patient record to gather this information.

#### **4.1.5 Termination of Study**

This study may be terminated at any time by the principal investigator (PI) in consultation with the Antibacterial Resistance Leadership Group (ARLG).

## 5 STUDY PROCEDURES

### 5.1 Data Collection

- Data will be collected on the following topics:
- Feasibility
- Strategies
  - PharmD chart and prescription review
  - PharmD/Prescriber communication
  - PharmD follow-up
- Pharmacist time
- Pharmacist and Prescriber perceptions (questionnaires)
- Secondary/Exploratory Objectives: DASON database (Pharmacy data, Admit/Discharge Table, Billing ICD9, Microbiology Lab, Bed Flow)
- The PharmD will provide patient data from two time points: first contact and at the time of discharge. In strategy 1, first contact will be the PharmD/prescriber contact and discussion. In strategy 2, first contact will be the date of the PharmD review (approximately 72 hours after the targeted antibiotic was started).

#### Endpoints

##### Primary endpoints (measured at the hospital level):

- Approval of interventions by hospital administration and committees
- Successful completion of training of a local PharmD
- Initiation of the intervention protocols

##### Secondary endpoints (measured at the patient level):

- DOT for each of the targeted and alternative antibiotics
- Duration of hospitalization
- Admission to the ICU (yes/no)
- Duration in ICU
- Discharged vs. death
- Benefit: risk measures to be developed as composites of other outcomes (details provided in an analysis plan)

##### Exploratory endpoints (measured at the patient level):

##### Comparison of utilization outcomes

348 Data Monitoring

349 No formal interim analyses involving hypothesis testing are planned. Data from the  
350 retrospective portion of the study will be cleaned and transmitted upon completion to conduct  
351 further cleaning and prepare for analyses.

352 Pharmacists will be provided with a data entry guideline (DEG) to ensure consistent data  
353 collection across participating hospitals.

354 **5.2 Other Study Procedures**

355 We will not enroll subjects as part of this protocol. Therefore, the following sections are not  
356 applicable:

357 Screening

- 358 1. Enrollment/baseline
- 359 2. Follow-up
- 360 3. Final study visit
- 361 4. Follow-up safety phone call
- 362 5. Early termination visit
- 363 6. Unscheduled visit
- 364 7. Laboratory evaluations

365        **6   STUDY PRODUCT DESCRIPTION**

366   Not applicable

367   **6.1   Concomitant Medications/Treatments**

368   Not applicable

## **7 ASSESSMENT OF SAFETY**

We are not enrolling patients; therefore, the following sections are not applicable:

1. Specifications of safety parameters
2. Methods and timing for assessing, recording, and analyzing safety parameters
3. Guidelines for assessing intensity of an adverse event (AE)
4. Guidelines for determining causality
5. Discontinuation due to AEs
6. Reporting procedures (for AE)
7. Type and duration of follow-up of participants after AEs
8. Halting rules
9. Safety oversight

## 8 CLINICAL MONITORING

ICH E6 states that the purpose of monitoring is to ensure the rights of subjects, obtain accurate data, and conduct the trial in accordance with protocol and applicable regulations. For the purposes of this protocol, a monitoring plan will be developed to ensure that three areas are adequately addressed.

Key areas that will be outlined will be the qualification of hospital personnel to conduct the trial, regulatory requirements (e.g. institutional review board [IRB] review), protocol training, data quality monitoring procedures, hospital data completion expectations (e.g. completeness, frequency), and pathways for issue escalation as well as for resolving any general questions at the hospitals.

## 9 STATISTICAL CONSIDERATIONS

### 9.1 Design and Sample Size Considerations

This is a feasibility study to evaluate if four hospitals can implement two antimicrobial stewardship interventions. Analysis of the primary feasibility components will be descriptive (a summary as to whether each hospital was able to successfully implement each of the interventions). No hypothesis testing will be completed for these summaries.

The secondary stewardship analyses may include hypothesis testing and estimation of the difference to the control as well as between the two stewardship strategies.

This study will collect data on all patients prescribed a targeted or alternative antibiotic at each of four hospitals, except patients who receive < 24 hours of surgical prophylaxis. The three targeted antibiotics are:

- Anti-pseudomonal carbapenem of choice at the study hospital
- Vancomycin
- Piperacillin-tazobactam.

The alternative antimicrobials of interest are:

- Fluoroquinolones
- Cephalosporins
- anti-MRSA systemic antimicrobials (e.g., nafcillin, daptomycin, linezolid, ceftaroline, clindamycin, and TMP-SMX).

This study will not target a specific number of patients to enroll. Instead, it will be conducted for specific periods of time. Each hospital will implement its first strategy for six months, followed by an one-month period with no strategy, and then a second, six-month period for the second strategy, for a total duration of 13 months. Additionally, one year of historical data from the four hospitals will be analyzed.

Although this study does not target a specific number of participants, hospitals are expected to admit at least 600 patients per month. Thus, we expect to have at least 3600 patients included in analyses for each six-month intervention period. When conducting within-hospital analyses, a conservative sample size of 3000 patients during each intervention period will achieve 97% power to detect a difference between the group proportions (e.g., of patients with no [0] DOT) of 0.0500 when the proportion in one group is 0.50 using an alpha of 0.05. The power for detecting a difference as a function of sample size is illustrated in Figure 9-1:

Figure 9-1:

[figure not shown]

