#### 9.4.1.3 Discussion of cluster randomized design and the key secondary analysis

This antimicrobial stewardship study will be implemented at four hospitals, where each hospital is considered a single cluster. The four hospitals participating in this study will be paired by size. One hospital in each pair will receive Strategy 1 followed by Strategy 2, while the other hospital in each pair will receive Strategy 2 followed by Strategy 1. The ordering within each pair will be randomly assigned.

Cluster randomized trials can be analyzed at the cluster level or the patient level. Ideally, analyses are conducted on the cluster level as this is the unit of randomization. However, we will analyze this study using the patient as the unit of analyses as there are only four clusters.

Since randomization occurs at the cluster level but analyses must be conducted at the patient level, the benefits of randomization (i.e., expectation of balance of confounding factors) cannot be assumed. The small sample size of 4 clusters may also negate the benefits of randomization. The crossover nature of the design will help to balance confounding factors as each hospital can serve as its own control. However, as the crossover occurs at the cluster level, and the patients are neither randomized nor crossed-over, it does not have the same advantages as a standard crossover trial and it does not eliminate within-patient variation; the analyses cannot be “paired”.

Since the effect of the intervention is not only a function of the intervention itself but also of the pharmacist, there is potential for considerable site variation in response. Thus each of the four sites will be evaluated separately. Stratified pooled analyses may also be conducted.

For each site and each contrast (Intervention 1 vs. control; Intervention 2 vs. control; and Intervention 1 vs. Intervention 2), the difference in outcomes will be estimated using 95% confidence intervals. Examples for binary and continuous outcomes are displayed in Figure 9-2 and Figure 9-3, respectively.

Figure 9-2

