408         than one intervention over the course of a year)

409 Signs and symptoms

410     • Fever

411     • Leukocytosis

412     • Hypotension

413     • Cough or Sputum production

414     • Other signs or symptoms

- 415 • List of other/specifies
- 416 • Number of signs and symptoms per intervention

417 Culture data

- 418 • Culture data available for review (yes/no)
- 419 • If yes, was the culture data reviewed
- 420 • If yes, did it help inform the recommendation?

421 Intervention outcome

- 422 • Was the recommendation followed?
- 423 • Was there an ID consult after the intervention?
- 424 • ICU admission

425 Ultimate Infection diagnosis related to recommendation

- 426 • Pneumonia
- 427 • UTI
- 428 • Meningitis
- 429 • Surgical site infection
- 430 • SSTI
- 431 • Colitis
- 432 • Bacteremia
- 433 • Sepsis with unknown source
- 434 • No infection
- 435 • Other
- 436 • List of other, specify

437 **10. Days Of Therapy**

438 **Purpose:** To address Secondary objective 2, to compare DOT for antibiotics of interest between each  
439 strategy.

440

- 441 • Days of therapy (DOT) for targeted and alternative antibiotics
  - 442 ○ Per the protocol, DOT will be measured as the number of days a patient receives
  - 443 each targeted and alternative antibiotic during the hospital admission

444 The three targeted antibiotics are:

- 445 • Anti-pseudomonal carbapenem of choice at the study hospital
- 446 • Vancomycin
- 447 • Piperacillin-tazobactam.

448 The alternative antimicrobials of interest are:

- 449 • Fluoroquinolones
- 450 • Cephalosporins
- 451 • anti-MRSA systemic antimicrobials (e.g., nafcillin, daptomycin, linezolid, ceftaroline,
- 452 clindamycin, and TMP-SMX).

Among admissions with an included antibiotic, by hospital

- Table 1
  - Year prior to study
  - Period 1 Admission with Included antibiotic, no intervention
  - Period 1 Admission with stewardship intervention
  - Period 2 admission with Included antibiotic, no intervention
  - Period 2 admission with stewardship intervention
- Table 2
  - Period 1 (all admissions with an antibiotic of interest)
  - Period 2 (all admissions with an antibiotic of interest)
- Table 3
  - For 3 contrasts (PAR vs Historical year; Res/PreA vs historical Year; PAR vs Res/PreA)
  - Difference in proportion used drug with 95%CI
  - Difference in Mean DOT with 95% CI

For each antibiotic,

- proportion of admissions where the antibiotic was received
- DOT for the antibiotic

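### Protocol section 9.1 counts admissions as analysed patients, so its 97% within-hospital power is correct arithmetic on an unsupported sample size

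*Combined protocol and SAP*

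**What the plan says.** Protocol section 9.1 sets no target number of patients and fixes the duration instead. It says that "hospitals are expected to admit at least 600 patients per month" and continues: "Thus, we expect to have at least 3600 patients included in analyses for each six-month intervention period". For within-hospital comparisons it then states that "a conservative sample size of 3000 patients during each intervention period will achieve 97% power". The effect behind that figure is an absolute difference of 0.05 from a proportion of 0.50, at alpha 0.05, with zero DOT as the example outcome.

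The same section defines a narrower population: "This study will collect data on all patients prescribed a targeted or alternative antibiotic at each of four hospitals", with patients given under 24 hours of surgical prophylaxis left out. Section 4.1.2 repeats both limits. SAP section 10 sets its days-of-therapy tables "Among admissions with an included antibiotic, by hospital", and SAP section 13 uses the same restriction for patient outcomes. SAP section 6 lists three separate counts: (a) all admissions, (b) admissions with an included or other antibiotic, and (c) admissions with an included antibiotic.

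On the unit of analysis, protocol section 9.4.1.3 says "we will analyze this study using the patient as the unit of analyses as there are only four clusters". It evaluates each site separately and, for exploring heterogeneity, models period by site as a random effect.

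**The concern.** The figure of 3,600 is SAP count (a), all admissions. The analyses use count (b) or (c). Section 9.1 therefore presents as analysed a number that its own eligibility rule reduces by an unstated amount. The 97% rests on 3,000, which is offered as a cautious allowance on 3,600, so its support depends on the same step.

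The power statement also has no term for a hospital's outcome shifting between periods. Within one hospital each strategy occupies a single period, so such a shift cannot be separated from a strategy effect. The plan expects such shifts: it models period by site as random, and SAP section 3.5.2 reports drug shortages and says temporal effects may differ between the two study periods.

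A site-level null result read against 97% power would look like good evidence of no difference when it may not be. Protocol section 10 also intends the study to inform power calculations for later cluster-randomized trials, so a loose denominator could carry forward.

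**Working it through.** **Inputs from section 9.1.** 600 admissions a month (read as per hospital, as the within-hospital use requires); six months per strategy; 3,000 per period; proportions 0.50 and 0.55; alpha 0.05. Sidedness is not stated; two-sided is assumed because the plan reports 95% intervals.

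**Inputs not in the documents.** The share of admissions that is eligible, and the SD of a hospital's true proportion from period to period. Both are assumed and shown as ranges.

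**1. Reproduce the 97%.** For n per period and independent patients, power = Φ[(0.05 − 1.96 × SE0) / SE1], where SE0 = √(2 × 0.525 × 0.475 / n) and SE1 = √((0.50 × 0.50 + 0.55 × 0.45) / n).

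At n = 3,000, SE0 = 0.01289 and SE1 = 0.01288, so power = Φ(1.92) = 97.3%. The stated figure reproduces. A one-sided test would give 98.7%, and 1,500 per period 78.3%.

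**2. What 97% requires.** 600 × 6 = 3,600 admissions. The chosen 3,000 is 3,000 / 3,600 = 83% of them. Solving the formula for 97% gives about 2,940 per period, and 2,940 / 3,600 = 82%.

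**3. Power by eligible share (assumed), no period variation.**

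| Share of 3,600 | n per period | Power, strategy vs strategy |
|---|---|---|
| 80% | 2,880 | 96.7% |
| 70% | 2,520 | 94.5% |
| 60% | 2,160 | 90.9% |
| 50% | 1,800 | 85.2% |
| 40% | 1,440 | 76.7% |
| 30% | 1,080 | 64.3% |

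Against the 12-month control the comparator is about twice as large, so less is lost: 93.5% at 1,800 vs 3,600, and 76.7% at 1,080 vs 2,160.

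**4. Period-to-period variation (assumed SD τ).** The between-hospital component cancels within a hospital, but the period component does not. It adds 2τ² to the variance of the difference, under both SE0² and SE1².

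At n = 3,000 and τ = 0.01, SE0 = √(0.00016625 + 0.0002) = 0.01914 and power = Φ(0.65) = 74.3%. Other values:

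| τ (percentage points) | Power, n = 3,000 | Power, n = 1,800 |
|---|---|---|
| 0 | 97.3% | 85.2% |
| 0.5 | 92.5% | 79.0% |
| 1 | 74.3% | 62.9% |
| 2 | 36.3% | 33.1% |

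These powers are for a test that allows for τ. If it is ignored at n = 3,000, a nominal 5% test has a false-positive rate of about 19% at τ = 1 point and 42% at 2 points.

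**The case against.** The strongest reply is that little depends on this number. The primary analysis is descriptive, with no hypothesis test; secondary analyses only may include testing; duration is fixed; and the SAP makes no power claim. Both documents call the study essentially non-randomized and admit that the short period and few sites limit the secondary analyses. This stands and lowers the severity. It does not correct the sentence, because no other section revises the 3,600 or qualifies the 97%.

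Other points also stand. The 600 a month is a floor and the hospitals range from 102 to 373 beds, so the 82% threshold applies at that floor only. A proportion of 0.50 is close to the worst case: for 0.10 vs 0.15 at 1,080 per period, the same formula gives 94%. Figure 9-1 plots power against sample size and is not visible in the copy reviewed, so smaller numbers may be shown there. The text still does not say which number applies.

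A reader might infer four stronger things that the documents do not support:

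- **That the 97% counts every admission.** It uses 3,000, which already drops 17% of 3,600. Only the 3,600 sentence makes that equation.
- **That the design fails to deliver 97%.** The eligible share and the period SD are not given, so failure cannot be shown.
- **That SAP section 10 narrows the set beyond the protocol's.** Included antibiotic is not defined. SAP section 6 sets it against other antibiotics, while a table under that heading in section 10 refers to any antibiotic of interest. It may mean targeted plus alternative drugs, or fewer.
- **That rewriting section 9.1 would cure site-level intervals that ignore period shifts.** Those intervals use the actual counts. The rewrite only makes the assumption visible.

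**Conclusion.** Wrong as written, of moderate severity. Section 9.1 states as analysed a count of admissions that its own eligibility rule, section 4.1.2 and the SAP tables all restrict. The 97% built on it is arithmetically sound but unsupported: at 600 admissions a month it holds only if about 82% or more of admissions are eligible and there is no hospital-by-period variation.

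The size of any shortfall depends on assumptions. An eligible share of 30 to 60% puts power for the direct strategy comparison at 64 to 91%, with smaller losses against the historical year. The period-variation figures are illustrations. With one period per strategy in each hospital, that SD cannot be estimated within a site, so independence is a caveat to state and not a demonstrated error.

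The zero-DOT example does not remove the problem. The SAP scores zero per antibiotic, within admissions that already received a study antibiotic. If all admissions were the intended denominator, section 9.1 would contradict section 4.1.2 and the SAP and would still need correcting.

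**What to change.** Rewrite the last paragraph of protocol section 9.1:

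1. Replace 3,600 with the expected eligible admissions per hospital per six-month period: half the historical-year count for the set actually analysed, after removing short surgical prophylaxis. Use the SAP section 6(b) count if that set is all targeted or alternative antibiotics, or 6(c) if it is included antibiotics only. Say which, and define included antibiotic.
2. Restate the power at that number for each hospital, separately for the strategy comparison and for the contrasts with the 12-month control.
3. State that the figure assumes independent patients and no hospital-by-period variation, and show its sensitivity, for example at period SDs of 1 and 2 percentage points (74% and 36% at n = 3,000).

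Alternatively, delete the power claim and present the within-hospital contrasts as estimation only, with the same caveat on period variation beside the intervals.

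The cost is one paragraph and a count the SAP already plans to produce. Conduct and data collection do not change. The downside is that the stated power will probably be less favourable.
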